## **2.1 Selection and Enrollment of Participants**

### **Inclusion Criteria:**

Patient inclusion criteria are as follows: Age  $\geq 65$ , bonded to a PCP in the KPCO Denver-Boulder geographic area, a diagnosis of ADRD or MCI from ICD-9 or ICD-10 visit codes or from the EHR problem list, one or more additional chronic conditions from a list 86 chronic medical conditions, and be taking 5 or more chronic medications (defined as a 28+ days' supply of medication on the eligibility date; excluding non-indicated medications such as vaccines and anesthetics based on 2-digit GPI codes).

Clinician inclusion criteria: Being a PCP for adult patients at the in the Denver-Boulder geographic area.

Care partner participation: As the intervention is designed to address the needs of the ADRD and MCI population, care partners of patients meeting eligibility criteria may serve as proxy respondents to rPATD materials and as partners during visits with PCPs.

Exclusion Criteria: As the pragmatic trial will be based in primary care clinics, individuals residing in long term care facilities or enrolled in hospice care at baseline will be excluded. We will also exclude individuals residing at home but receiving all their primary care through the Home Rounding service which replaces primary care delivery.

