### 490 Definitions

of assessment variables from Schedule 4.1 above and associated data elements and sources are itemized

below. Unless otherwise mentioned, all data will be extracted from the KPCO Virtual Data Warehouse, a quality controlled, common data model that includes data from multiple KPCO data sources covering the following domains: Enrollment, utilization, pharmacy, tumor registry, demographics, lab results, mortality, vital signs, census data, geocoded demographic data, patient reported outcomes collected in the course of care, problem list diagnoses, and social history.

Inclusion/ exclusion criteria: as previously described. Data elements will include age, diagnosis codes, location of primary care provider, current medications. Chronic diagnoses will be from a list of 86 chronic conditions itemized in the Multiple Chronic Conditions Chartbook (Gerteis J, et al.). We have developed a method of counting chronic medications that utilizes the Generic Product Index (GPI) in a manner similar to prior work using the WHO Anatomic Therapeutic Chemical index A. Study experts ([name], [name], [name], [name], [name]) created a consensus-based list of GPI categories to be included in estimating the criterion of 5 or more chronic medications (this list excludes drug classes unlikely to be used as chronic medications, such as vaccines and anesthetics).

Demographics: age, gender, self-reported race/ethnicity from the EHR, census-based socioeconomic status.

Diagnoses: ICD-9 (historical) and ICD-10 codes will be used to identify diagnoses from visit billing codes, hospital and emergency department claims, and problem list diagnoses.

Current chronic medications: Total number of chronic medications on the date of study eligibility. Chronic medication use is defined as any medication for which the patient had at least a 28-day supply on the baseline eligibility date. We selected a 28-day supply (rather than a supply for a longer time period) because opioid medications are often dispensed in 28-day supplies. All current medications exclude the following domains identified by 2-digit GPI codes: Vaccines, Toxoids, Allergenic extracts, Oxytocics, Local anesthetics – parenteral, General anesthetics, Antiseptics and disinfectants, Antidotes, Diagnostic products, Chemicals, and Medical devices.

Primary Outcomes:

Number of drugs: number of chronic medications – see above.

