## **7.4 Outcomes**

Primary outcomes are number of chronic medications and percent of individuals on one or more potentially inappropriate medications (PIMS).

Secondary outcomes to be addressed following primary analyses include the number of starts of potentially inappropriate medicines, dose reductions for selected potentially inappropriate medications (benzodiazepines, opiates, and antipsychotics), rates of adverse drug events (falls, hemorrhagic events, and hypoglycemic events), activities of daily living as reported in the Medicare Health Risk Assessment, and skilled nursing facility, hospital, and emergency department admissions.

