## **7.5 Data Analyses**

The distributions of all variables, including outcomes, predictors, and covariates, will be examined univariately for data integrity, missing data, and outliers. Outliers will be explored with limited chart review. Data transformation may be conducted as appropriate. We will then assess bivariate associations between independent variables, covariates and primary and secondary outcomes. Multilevel models will be used to account for the clinic level randomization and clinic level intervention as well as adjusting for covariates. The models will include random effects for clinic and fixed effects for intervention versus delayed control and time (baseline or 1-year). We will assess possible nesting of patients within providers; however, most patients see multiple medical doctors, physician assistants and/or nurse practitioners. Change in medication use will be estimated in models that examine medication outcomes at follow-up, adjust for baseline medication use and estimate change by including an interaction term for intervention by time. These models can include baseline patient risk factors as well as provider characteristics to account for imbalanced baseline covariates between clinics. Primary analyses will focus on all members meeting eligibility at either baseline or follow-up time periods (6-months and 1 year) and patient indicators will be included as random effects to identify which patients have information at both baseline and follow up versus baseline or follow up only. Secondary analyses will examine the subset of patients who have both baseline and follow-up data available. We expect these secondary analyses will have comparable conclusions but if differences are seen we will explore potential explanations such as unexpected differential deaths or loss-to-follow-up or whether differences in the patient populations might suggest effect modifiers. For change in number of chronic medications, we expect to use Poisson regression mixed models while for change in the proportion of patients on PIMs, and some secondary outcomes, nonlinear

mixed model techniques will be needed. These models already accommodate data that are missing at random (MAR), which will be adequate for some missing covariate data. For items unlikely to be MAR, such as missing questionnaire responses, we will explore multiple imputation methods to estimate missing scores.

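### Section 7.5 admits members to the primary analysis by eligibility at follow-up, so part of the set is selected after randomisation on the medication count, a primary outcome

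*Protocol*

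**What the plan says.** Section 7.5 of the Protocol defines the primary analysis set: "Primary analyses will focus on all members meeting eligibility at either baseline or follow-up time periods (6-months and 1 year". It expects some members to contribute at one time only, since patient random effects are meant to show "which patients have information at both baseline and follow up versus baseline or follow up only". The models are to "examine medication outcomes at follow-up, adjust for baseline medication use and estimate change by including an interaction term for intervention by time". A further analysis is narrower: "Secondary analyses will examine the subset of patients who have both baseline and follow-up data available".

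Under section 2.1 an eligible patient must "be taking 5 or more chronic medications". Section 7.4 states the outcomes: "Primary outcomes are number of chronic medications and percent of individuals on one or more potentially inappropriate medications". Section 4.2 defines current chronic medications as the "Total number of chronic medications on the date of study eligibility", and the primary outcome on number of drugs refers back to that definition. The eligibility threshold and the first primary outcome therefore use the same variable.

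Elsewhere the Protocol describes a cohort fixed at baseline. The schedule in section 4.1 applies the inclusion and exclusion criteria only when the eligible population is identified. Section 4.2 sets baseline at the mailing (intervention clinics) or at the first primary care appointment in the initial intervention period (control clinics), and times follow-up from there.

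**The concern.** Membership of the primary set depends partly on a post-randomisation value of the outcome. Someone on 4 medications at baseline who has 5 or more at 6 or 12 months joins the set, and the same person staying at 4 does not. If the intervention lowers counts, fewer people cross the threshold in intervention clinics than in control clinics. The two arms then differ in who was admitted, and randomisation of clinics does not protect against that.

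The direction can be seen directly. Let m0 and m1 be the follow-up means of baseline-eligible members (control, intervention), e0 and e1 the means of follow-up-only entrants, and w0 and w1 the entrants' shares of each set. The difference in follow-up means is

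(m1 − m0) + w0(m0 − e0) − w1(m1 − e1).

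Entrants come in near the threshold, so they have lower counts than the baseline-eligible members and pull both means down. The control mean is pulled down more, because w0 exceeds w1 and m0 exceeds m1. The two extra terms together are positive, and a true decrease looks smaller.

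At stake is the size of the estimated effect on medication count, and the match between the analysed set and the cohort described in the rest of the Protocol.

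**Working it through.** **The Protocol's own figure (section 7.2).** Inputs: 3,671 members, 18 clinics, rate 6.8, decrease 0.70, ICC 0.01, power above 80%. The section states neither alpha nor sidedness; two-sided 0.05 is assumed.

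- Mean clinic size: 3,671 / 18 = 203.9.
- Design effect: 1 + 202.9 × 0.01 = 3.029.
- Effective members per arm: 1,835.5 / 3.029 = 605.9.
- Standard error: √((6.8 + 6.1) / 605.9) = 0.146; z = 0.70 / 0.146 = 4.80.
- Power: Φ(4.80 − 1.96) = 99.8%.

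The statement of more than 80% holds. It fixes the effect size used below.

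**Effect of the analysis set.** The Protocol gives no rates of stopping or starting medications, so these are assumptions. Each patient has a latent mean from a gamma distribution and a Poisson baseline count. At follow-up each medication is stopped with a given probability, and new starts are Poisson at the same rate times the latent mean. In the intervention arm the stop probability is raised by 0.70 divided by the mean baseline count among eligible members, so the true effect among the baseline-eligible is about −0.70. There were two million patients per setting. The mean baseline count among those on 5 or more was 6.59 to 6.69, against the Protocol's 6.8.

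Four estimates are compared:

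- A: set fixed by baseline eligibility, all follow-up counts kept.
- B: eligible at either time, baseline-eligible members always kept, follow-up means compared (entrants' baseline counts unused).
- B+: as B, but change from baseline, using entrants' baseline counts.
- C: a follow-up record counts only if it is again 5 or more.

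| Latent mean, shape | Stop and start rate | A | B (share of A) | B+ (share) | C (share) | Entrants, control / intervention |
|---|---|---|---|---|---|---|
| 4.0, 8 | 8% | −0.698 | −0.616 (88%) | −0.694 (99%) | −0.218 (31%) | 9.4% / 6.5% |
| 4.0, 8 | 15% | −0.701 | −0.592 (84%) | −0.697 (99%) | −0.217 (31%) | 13.9% / 10.2% |
| 3.2, 3.2 | 15% | −0.700 | −0.586 (84%) | −0.694 (99%) | −0.208 (30%) | 14.2% / 10.5% |
| 4.0, 8 | 25% | −0.698 | −0.576 (82%) | −0.695 (100%) | −0.217 (31%) | 18.2% / 14.1% |
| 3.2, 3.2 | 25% | −0.702 | −0.571 (81%) | −0.699 (100%) | −0.207 (30%) | 18.5% / 14.4% |

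The entrants' share differs by arm in every row. Under B the loss is 12–19%; under B+ it is 0–1%; under C it is about 70%. Across these settings 10–23% of baseline-eligible control members and 26–35% of intervention members fall below 5 at follow-up, which is why C costs so much.

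**Linear mixed model**, patient random intercept, arm-by-time interaction, 40,000 patients, second row's settings:

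- A: −0.68.
- Either time, both records used: −0.66.
- Either time, entrants without a baseline record: −0.65.
- C: −0.39.

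From the unrounded estimates, the loss under either version of B is about 4% (1 − 0.653 / 0.683), and under C about 43% (1 − 0.388 / 0.683).

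**Other assumed count distributions and persistence rates.** These give a 5–19% or 8–13% loss on the literal reading and 46–69% under C. Entrants can be as few as 5% of the control set and 3% of the intervention set.

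**The planned secondary analysis.** If having data at both times meant being on 5 or more at both times, the change estimate in the five settings would keep only 68–74% of A. It is therefore not a sure safeguard.

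**The case against.** The strongest reply is that section 7.5 says *either*. A member eligible at baseline who goes from 5 medications to 4 still meets that condition and stays in the set. A reader might infer that the set hides successful deprescribing; the wording does not support that. The large loss needs a record-level rule that appears nowhere, and the context leans against it. Section 7.5 speaks of available information and names deaths and loss to follow-up as possible explanations. Section 4.2 ties the medication count to the baseline eligibility date, and section 6 has outcomes collected whether or not deprescribing is discussed. This objection stands. What remains is that the text never says follow-up counts below 5 are kept.

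Four further points stand:

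- Entrants need not lack a baseline count. Counts come from dispensing data, which could supply one for a continuing member, and the bias then nearly disappears. Section 7.5 does not say that this will be done.
- The literal-reading bias does little to power. At −0.57, the standard error is √((6.8 + 6.23) / 605.9) = 0.147, z = 3.89, and power is Φ(3.89 − 1.96), about 97%.
- A reader might extend the bias to the outcome on potentially inappropriate medications. Use of such a medication is not an eligibility criterion, and no bias on that outcome has been calculated.
- A reader might take "These models already accommodate data that are missing at random (MAR), which will be adequate for some missing covariate data" as an error that makes the model drop entrants' rows. The sentence is hedged, and with an intervention-by-time term the baseline count may be an outcome row rather than a covariate. Row loss is not established.

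An open cohort analysed by assigned clinic is also a legitimate design when clinics are randomised. That does not answer the point, because the difficulty is the threshold on the outcome at entry, not the open cohort as such.

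**Conclusion.** The concern holds in a limited form. Follow-up-only entrants are selected after randomisation on a threshold of the first primary outcome, and the resulting bias in the medication-count effect is toward no effect. On the literal reading the attenuation is roughly 0–19%, near zero if entrants' sub-threshold baseline counts are used. It would be roughly 45–70% only if follow-up records had to show 5 or more again. These sizes rest on assumed stop and start rates (8–25% in the table) and assumed count distributions. The direction rests only on the entry rule and on the intervention lowering counts. The set also conflicts with the baseline cohort described in sections 4.1 and 4.2. Because the Protocol itself fixes the primary set, this is more than a detail left to a later document.

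**What to change.** In section 7.5, define the primary analysis set as all members who meet the eligibility criteria at the index (baseline) date given in section 4.2, analysed by the clinic's assigned arm. State that 6- and 12-month medication counts are used whatever their value, including counts below 5. Move members eligible only at follow-up to a sensitivity analysis, and say there how their baseline counts are obtained and used. State that the analysis of members with data at both times requires an available count, not renewed eligibility.

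The change needs Protocol wording only and no new data. Its cost is that follow-up-only records leave the primary analysis; in the simulations these were about 5–19% of the control set and 3–14% of the intervention set.

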Percent of individuals taking one or more PIMs: chronic medications that are listed as potentially inappropriate for older adults based on the Beers list plus opioid medications.

520 Secondary Outcomes:

521 Dose reductions: Because calculating dose reductions requires analyzing specific targeted medications, we  
522 will assess dose reductions in three selected drug classes. We selected these classes based on the premise  
523 that the medications posed risks of adverse side effects, but that patients, care partners, and clinicians may  
524 be reluctant to discontinue the medications for fear of recurrent symptoms. The three drug classes are  
525 benzodiazepines, opiates, and antipsychotics.

526 Adverse Drug Events: We will examine three types of ADEs that are common causes of emergency service  
527 use among older adults and that may plausibly be expected to decrease in a culture of thoughtful  
528 deprescribing. These are falls; hemorrhagic events; and episodes of hypoglycemia in individuals with  
529 diabetes. All of these outcomes will be calculated from ICD-10 diagnoses using code lists extracted from  
530 the literature and/or previously validated at KPCO. Rates will be calculated for the year prior to baseline  
531 and the year following the initial brochure mailing. Denominators will use person-years to account for  
532 changes in enrollment and deaths.

533 ADLs: Activities of Daily Living are reported by patients/ proxy responders as part of the annual Medicare  
534 Health Risk Assessment (HRA). These data will be available on the subset of patient participants who have  
535 completed the HRA. (Estimated at 45% of the KPCO Medicare beneficiary population.) Data from the most  
536 recent HRA will be used.

537 Hospitalization rate, emergency department visit rate, skilled nursing facility admission rate: Presence/  
538 absence of a one of these admissions over the year prior to baseline and post intervention. (We will  
539 distinguish between temporary and permanent admissions to skilled nursing facilities.)

540 Mortality: Death from any cause during the study period.

541 Additional planned evaluations:

542 Following the intervention, we will explore mechanisms of intervention effectiveness and uptake through  
543 post hoc qualitative interviews with patients, family caregivers, and clinicians; patient and clinician survey  
544 responses; and descriptions of outpatient office visit length. Data and variables include:

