We will examine effects of the intervention within the following prespecified subgroups: 1) members who received a higher dose of the intervention (e.g., brochure and more than one visit), 2) members on higher numbers of medications at baseline (7 or more medications), and 3) individuals with MCI vs. ADRD. We anticipate missing data on at least 50% of the cohort for secondary outcome measures of patient reported outcomes of ADLs and health related quality of life and analyses will use a three-pronged approach. First, we will describe persons with and without these measurements by covariates such as age, health care utilization and co-morbidities. Second, we will use multiple imputation to create replicate datasets with plausible values using estimation models that include covariates and the dependent variables themselves. Because multiple imputation can only address data that are missing at random, i.e. missing data explained by measured covariates, our third step will be sensitivity analyses using methods such as pattern mixture models that aid in examining the consistency of results within groups of patients with similar patterns of missing data.

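### Section 7.5 applies the mixed models' missing-at-random property to covariates, and offers multiple imputation for questionnaire items it calls unlikely to be missing at random

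*Protocol*

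**What the plan says.** All the statements are in Protocol Section 7.5.

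- **Models.** "For change in number of chronic medications, we expect to use Poisson regression mixed models", with nonlinear mixed models for the proportion on a PIM. On adjustment: "These models can include baseline patient risk factors as well as provider characteristics to account for imbalanced baseline covariates between clinics". The primary analysis set is every member who is eligible at baseline or at follow-up.
- **Missing covariates.** "These models already accommodate data that are missing at random (MAR), which will be adequate for some missing covariate data". No imputation and no model for the covariates is described alongside this.
- **Items thought not to be MAR.** "For items unlikely to be MAR, such as missing questionnaire responses, we will explore multiple imputation methods to estimate missing scores". No other method is named for these items.
- **The limit on imputation.** Two sentences into its plan for ADLs and health-related quality of life, the section says: "Because multiple imputation can only address data that are missing at random, i.e. missing data explained by measured covariates", and continues: "our third step will be sensitivity analyses using methods such as pattern mixture models". That plan is introduced for those two patient-reported measures only.

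Section 8.2 applies the word questionnaire to the rPATD and PPMD. It says their results will be used, within the intervention group, to relate outcomes to willingness to deprescribe.

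**The concern.** Two statements do not do what they are meant to do.

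First, a mixed model fitted by likelihood uses all observed outcomes and is valid when outcomes are missing at random given what is in the model. It has no distribution for its covariates. A record with a missing covariate contributes nothing unless something further is done. MAR is therefore the wrong reason for leaving missing covariates alone, and an analyst who follows the sentence would lose members from the set that the section defines as primary.

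Second, the section identifies a class of data as unlikely to be MAR and names for it only a method that it then says is limited to MAR data. The remedy it recognises, a sensitivity analysis outside MAR, is attached to other variables.

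At stake in the first case are some precision and, under one kind of missingness, some bias in the primary comparison. At stake in the second is the credibility of an exploratory analysis of mechanism.

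**Working it through.** The protocol states no covariate missingness and no questionnaire response rate, so there is no figure of its own to reproduce. The checks below are illustrations with assumed missingness, followed by a comparison of the text.

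**1. Does the MAR property carry over to covariates?**

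Inputs from Section 7.2: 3,671 members in 18 clinics (3,671/18 = 203.9, taken as 204 per clinic), mean count 6.8, effect −0.70. Assumed: a linear random-intercept model with one record per patient, a standard normal covariate with slope 1.00, clinic SD 0.2 and residual SD 1.5. The implied ICC is 0.04/(0.04 + 1.00 + 2.25) = 0.012, close to the planned 0.01. There were 400 simulated trials per row, and all fits converged. Records with the item missing were dropped.

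| Missing item, and what its missingness depends on | Missing | Intervention effect: full data → after deletion | Covariate slope: full data → after deletion |
|---|---|---|---|
| Outcome, on the observed covariate (MAR) | 34.0% | −0.690 → −0.694 | 0.999 → 0.998 |
| Covariate, on the observed outcome (also MAR) | 33.8% | −0.710 → −0.555 | 1.002 → 0.786 |
| Covariate, on its own value only | 34.0% | −0.697 → −0.697 | 1.000 → 1.001 |

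Monte Carlo standard errors are 0.004 to 0.006 for the effect and 0.001 to 0.002 for the slope.

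The first two rows are both MAR. Only the first is free of bias; in the second the effect shrinks by (0.710 − 0.555)/0.710 = 22%. The third row is not MAR, yet deletion is unbiased there, at the cost of a third of the records. So MAR is not the condition that decides whether leaving missing covariates to the mixed model is adequate. What matters is whether missingness depends on the outcome given the covariates.

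**2. What would the loss of records cost?**

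Inputs from Section 7.2: 35.8% against 29.0% on a PIM, and ICC 0.01. The section states that ICC for the medication count; using it for PIMs is an assumption. For a retained fraction f:

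- m = 3,671f/18
- design effect = 1 + (m − 1) × 0.01
- effective n per arm = (3,671f/2)/design effect
- power = Φ(0.068/SE − 1.96), with SE = √[(0.358 × 0.642 + 0.290 × 0.710)/effective n]

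At f = 1, SE = √(0.4357/606) = 0.0268, and power = Φ(2.54 − 1.96) = 72%.

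| Retained (assumed) | m | Design effect | Effective n per arm | Power |
|---|---|---|---|---|
| 100% | 204 | 3.03 | 606 | 71.8% |
| 95% | 194 | 2.93 | 596 | 71.0% |
| 90% | 184 | 2.83 | 585 | 70.2% |
| 80% | 163 | 2.62 | 560 | 68.4% |

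The loss is 0.8 to 3.4 points. It is small because clustering already limits the information per clinic. Only the differences between rows matter here: the 72% starting value follows from the planning inputs and the ICC assumption, not from the missing-data wording.

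**3. The two imputation statements side by side**

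| | Questionnaire responses | ADLs and quality of life |
|---|---|---|
| Stated mechanism | Unlikely to be MAR | MAR not assured |
| Method | Multiple imputation, to be explored | Description, then multiple imputation |
| Step outside MAR | None named | Pattern-mixture sensitivity analysis |

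The reason given for the last cell on the right, that imputation needs MAR, applies with more force to the column on the left, where MAR has already been called unlikely.

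**The case against.** The sentence on covariates is hedged: it speaks of some missing covariate data. The third row of the simulation shows that deletion can be harmless, so the sentence can be true in particular cases. Adjustment is optional, no adjustment covariate beyond baseline medication use is fixed, and that comes from dispensing records. The detail of covariate imputation commonly belongs in the SAP, which is not at hand. All of this stands and limits the weight of the point. It does not rescue the reason given, which would steer an SAP the wrong way.

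On the questionnaires, one can read the three-step plan for ADLs and quality of life as the elaboration of the preceding sentence, so that the step outside MAR is already supplied. The text leaves some room for that, since ADLs also come from a patient-completed assessment. But Section 8.2 uses the word for the rPATD and PPMD, and the three-step plan does not mention them. The plan for ADLs and quality of life is itself coherent and is not criticised here.

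Four stronger readings are tempting and not supported.

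- *The primary analysis is a complete-case analysis.* It becomes one only where a covariate with missing values is actually used.
- *A health risk assessment item among the covariates would leave fewer than half of members.* The relevant figure, "Estimated at 45% of the KPCO Medicare beneficiary population", stands with the ADL outcome in Section 4.2 and describes all Medicare beneficiaries of the plan. No section makes such an item a primary-model covariate.
- *Imputation is prescribed for non-MAR items.* The protocol says it will be explored, though it is the only method named.
- *The questionnaire problem can be sized as bias in the mean attitude score.* Section 8.2 uses the scores as predictors of outcome. Bias in a mean does not give bias in that association.

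**Conclusion.** The point holds in two limited parts.

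1. The MAR sentence gives a wrong reason for leaving some missing covariates to the mixed models. Its consequence is loss of members from the stated primary set wherever an incomplete covariate is used, with bias possible if missingness is related to the outcome. The extent cannot be derived from the protocol. The effect on the primary result is probably small: at an assumed loss of up to 20% of members, the PIM comparison loses about 3 points of power. The 22% shrinkage in the simulation needs outcome-dependent missingness in about a third of records, which nothing in the protocol suggests. It shows the mechanism and is not a forecast.

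2. Section 7.5 is inconsistent about multiple imputation for questionnaire items. This reaches only the exploratory analyses within the intervention group, and no primary or secondary outcome. Its size cannot be stated.

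These results rest on the assumed missingness models, a linear stand-in for the Poisson and nonlinear mixed models, equal clinic sizes, and the ICC of 0.01 carried over to PIMs.

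**What to change.** Change the two statements in Section 7.5 and carry the change into the SAP.

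1. **Covariates.** Confine the MAR statement to missing outcomes. Then state that no member leaves the primary model for a missing baseline covariate: such values are handled by multiple imputation whose model includes the outcome, the arm and the clinic, or, for categorical baseline covariates, by a missing category. Outcome and clinic must be in the imputation model, because leaving them out would weaken the covariate-outcome relation and ignore the clustering.

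2. **Questionnaire scores.** State that they are analysed in responders, or by imputation labelled as resting on MAR. Extend the pattern-mixture step already planned for ADLs and quality of life to these scores, with delta-adjusted values over a stated range. A responders-only analysis is a reasonable option here: the third row of the simulation shows that it preserves the association when non-response depends on the attitude itself and not further on the outcome.

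The cost is a few sentences and a little extra analysis work. No new data or participants are needed.
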